## Methods

### Study design

The ESCORT study is a community-based, cluster randomized controlled trial. Duration of the study is 2 years. This study has been conducted at Kamphaeng Phet Province, located about 400 kilometers north of Bangkok (Figure 1 and Figure 2). Due to strong relationship among neighboring households in rural communities, it is unable to assign subjects living in the same district to be randomly received either of the 2 CKD care programs without crossover interference from one subject in one household to another. As a result, we have conducted a cluster randomized controlled trial. Two out of eleven districts of the Province, namely Sai Thong Wattana District (control group) and Khlong Khlung District (intervention group), were randomly selected. Details of Public health characteristics of these 2 districts were described in Table 1.

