### Enrollment

The study was approved by the Ethics Committee of Institutional Review Board of Ministry of Public Health, Thailand and was registered with http://www.clinicaltrials.gov (NCT01978951). Written inform consents were obtained prior to recruitment. The study was conducted in accordance with good clinical practice and the Declaration of Helsinki [7]. Eligible cases are those who live in these 2 districts, age of 18–70 years old and had diabetes and/or hypertension. Patients whose eGFR was in a range of 15–59 ml/min/1.73 m^2^ body surface area estimated twice at 3 months apart were asked to participate in this study. Creatinine-based estimated glomerular filtration rate (eGFR) was calculated with the CKD-EPI equation [8]. Patients were excluded if they have any of the following: unstable/advanced cardiovascular disease, obstructive uropathy, ESRD, HIV infection, pregnancy, body mass index (BMI) less than 18 or more than 40 kg/m^2^, being under treatment for malignancy, urine protein-creatinine ratio more than 3.5 g/g creatinine and active urinary sediment (urine red blood cells more than 3 cells/high power field or urine white blood cells more than 10 cells/high power field). Hypertension was defined as a systolic blood pressure higher than 140 mmHg or a diastolic blood pressure higher than 90 mmHg or concomitant use of antihypertensive medications [9]. Blood pressure was recorded twice with a sphygmomanometer with 15-minute rest between the measurements. Diabetes was diagnosed when a fasting plasma glucose is at or above 126 mg/dl or HbA1C at or above 6.5 percent twice after repeated measurements [10].

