### Laboratory analysis

A protocol of laboratory investigation is summarized in Table 4. Prior to each hospital visit, all subjects will be instructed to have an 8-hour overnight fast. Plasma glucose, lipid profile, HbA1C, albumin, electrolytes, and urine analysis will be measured in the next morning. After centrifugation, plasma and urine samples will be centrifuged and transported at 4°C and analyzed within 24 hours at the laboratory Department of the District 2 Hospital. All blood chemistries will be measured with ABX Pentra 400 analyzer (HORIBA ABX S.A.S., France). Urine protein and creatinine will be measured with the pyrogallol red colorimetric method with the same analyzer. All biochemistry analyses will be validated according to the standard protocol of Department of Medical Sciences, Ministry of Public Health, Thailand. Serum creatinine will be measured by the enzymatic method. Serum creatinine measurement will be standardized with standard reference material (SRM 967) by commutability study at every 6 months [14].

Two out of twelve subgroups of both groups will be randomly selected and assigned to collect 24-hour urine. An aliquot of 24-hour urine of each sample will be sent for urine chemistry analysis protein, creatinine, urea, and sodium at Laboratory Department of Division of Nephrology, Chulalongkorn University, Bangkok, Thailand.

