### Outcomes

The primary outcome of this study is the difference of rate of eGFR decline. The secondary outcomes are laboratory parameters (Table 4) and incidence of clinical endpoints including all-cause mortality, cardiovascular events (acute myocardial infarction and stroke), ESRD (eGFR is less than 15 ml/min/1.73 m^2^), and 50% increase in serum creatinine from baseline. In this study, acute myocardial infarction is defined as a new ischemic pattern change of ECG and significant rising of cardiac enzymes. Acute stroke is defined as there is a clinical significant neurological deficit with an objective evidence by appropriate imaging study (e.g. computerized tomography scan). Patients will be followed at the first month and every three months after enrollment. Subgroup analysis will be done for selected parameters including age, sex, and diabetes mellitus. Quality of life will be assessed using a validated questionnaire, Thai SF-36 health survey [15].

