### Statistical analysis

Analysis of the primary outcome will be based on an intention-to-treat basis. Descriptive statistics will be expressed as the mean and standard deviation. Discrete variables will be presented as frequency and percentage. An independent t-test will be applied to compare mean values and mean differences between intervention and control groups. Differences between categorical variables will be analysed with Chi-square or Fisher’s exact tests. The comparison of the rate of eGFR decline will be analyzed using linear mixed models (Generalized Estimating Equation) [16]. The difference of incidence of clinical endpoints will be analysis using Cox-regression analysis. All statistical tests will be two-tailed tests. A P-value of less than 0.05 will be considered statistically significant. The data will be analysed using SPSS 16.0 (SPSS Inc., Chicago, IL, USA).

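### The unadjusted t-test on mean HbA1c pools patients with and without diabetes, so it is sensitive to a district difference in diabetes prevalence

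*Protocol article*

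**What the plan says.** - **Who enters.** Under Enrollment, eligible patients "had diabetes and/or hypertension", so hypertension without diabetes is enough. The share with diabetes is not given, overall or by district.
- **What is measured.** Table 4 schedules HbA1c at months 0, 6, 12, 18 and 24. Neither the table nor the Laboratory analysis section limits it to patients with diabetes. The same section does limit the 24-hour urine collection to two of the twelve subgroups.
- **Its status.** Under Outcomes: "The secondary outcomes are laboratory parameters (Table 4) and incidence of clinical endpoints".
- **The test.** Under Statistical analysis: "An independent t-test will be applied to compare mean values and mean differences between intervention and control groups". No covariate is named. Tests are two-tailed, and "A P-value of less than 0.05 will be considered statistically significant".
- **The groups.** Under Study design: "Two out of eleven districts of the Province, namely Sai Thong Wattana District (control group) and Khlong Khlung District (intervention group), were randomly selected". Each arm is therefore one district.
- **Subgroups.** Under Outcomes: "Subgroup analysis will be done for selected parameters including age, sex, and diabetes mellitus". HbA1c is not named there.

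**The concern.** HbA1c differs between people with and without diabetes before any treatment starts. In a mixed sample, the group mean therefore depends partly on how many patients with diabetes each district enrolled. With one district per arm, nothing in the allocation makes those shares alike, and Table 1 gives no diabetes figures. A t-test on follow-up means allows for chance variation in case mix between samples from the same population. It does not allow for a real difference in prevalence between two districts.

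The size of the effect is a second matter. If the programme lowers HbA1c mainly in patients with diabetes, the whole-group difference is that effect multiplied by their share. A reader who wants to know what the programme does for glycaemic control in diabetes would not find the answer in the pooled figure. Glycaemic control is one plausible route from the programme to slower eGFR decline, so the HbA1c result helps to interpret the primary outcome.

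**Working it through.** The article gives no figure for HbA1c to reproduce; its sample size concerns eGFR decline. What follows is an illustration.

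**From the article:** 433 enrolled, 15% loss, two-sided 0.05, one district per arm. With an assumed equal split, 433 × 0.85 / 2 = 184 per arm.

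**Assumed:**
- HbA1c 7.5 (SD 1.5) with diabetes and 5.6 (SD 0.4) without.
- True effect 0.5 points, in diabetes only.
- SD of change 1.3 with diabetes and 0.3 without.
- Diabetic share p from 30% to 70%.
- Patients independent, as the t-test itself supposes.

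**1. Sensitivity to case mix, with no treatment effect.** Shift in mean values = prevalence gap × (7.5 − 5.6).

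Pooled variance = p × 1.5² + (1 − p) × 0.4² + p(1 − p) × 1.9². At p = 0.5 this is 1.125 + 0.080 + 0.9025 = 2.1075, so SD = 1.45 and SE = 1.45 × √(2/184) = 0.151.

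For a 10-point gap the shift is 0.10 × 1.9 = 0.19. Then 0.19 / 0.151 = 1.26, and the chance of P<0.05 is about 24%. The shift would already be present at month 0.

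On change from baseline the fixed gap of 1.9 cancels. What is left is the prevalence gap × any change common to patients with diabetes in both arms. With an assumed common change of −0.3, this is 0.10 × 0.3 = 0.03 in size. Variance of change = 0.5 × 1.3² + 0.5 × 0.3² = 0.89, so SD = 0.943 and SE = 0.098. Then 0.03 / 0.098 = 0.30, and the chance is about 6%.

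| Prevalence gap (average share 50%) | Mean values: shift, chance of P<0.05 | Change from baseline: shift, chance of P<0.05 |
|---|---|---|
| 5 points | 0.095, 10% | 0.015, 5% |
| 10 points | 0.19, 24% | 0.03, 6% |
| 20 points | 0.38, 72% | 0.06, 9% |

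With the average share at 30% or 70% instead, the 10-point row gives 31% or 22% on mean values and 7% or 6% on change.

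**2. Size of effect and power.** Whole-group effect = 0.5p. The diabetes-only comparison has 184p patients per arm.

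At p = 0.5 on mean values:
- Pooled: 0.25 / 0.151 = 1.65, power 38%.
- Diabetes only: SE = 1.5 × √(2/92) = 0.221, and 0.50 / 0.221 = 2.26, power 62%.

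At p = 0.5 on change:
- Pooled: 0.25 / 0.098 = 2.54, power 72%.
- Diabetes only: SE = 1.3 × √(2/92) = 0.192, and 0.50 / 0.192 = 2.61, power 74%.

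| Diabetic share | Whole-group effect | Power on mean values: pooled vs diabetes only | Power on change: pooled vs diabetes only |
|---|---|---|---|
| 30% | 0.15 | 21% vs 42% | 48% vs 52% |
| 50% | 0.25 | 38% vs 62% | 72% vs 74% |
| 70% | 0.35 | 59% vs 76% | 86% vs 87% |

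On mean values, pooling costs power and exposes the result to case mix. On change from baseline both problems are small, although the pooled estimate is still 0.25 where the effect in diabetes is 0.50.

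**The case against.** **Nothing says that HbA1c is analysed over all patients.** This is the strongest objection. The t-test sentence is generic, and an article may leave analysis sets to a fuller document. It stands in part: an explicit decision to pool HbA1c cannot be attributed to the sponsor. But the article does name the outcome, the test and the groups, and taken together they give the pooled, unadjusted comparison.

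**Change scores deal with it.** A reader might infer that any prevalence difference must read as a treatment effect. The documents do not support that. The same sentence also covers mean differences; if these are changes from baseline, which the article does not define, the fixed gap cancels and little bias is left. The problem lies with the mean values, which are also to be tested.

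**A diabetes subgroup is already planned.** That is so, and it supplies most of the remedy. It is not tied to HbA1c, however, and as a subgroup result it would rank below the pooled one.

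**A smaller whole-group effect is not a biased one.** This stands. The pooled difference estimates the average over all enrolled patients, which is a different quantity from the effect in diabetes. Table 2 also lists its HbA1c target for both groups without limiting it to diabetes, so the article cannot be cited as saying that HbA1c matters only in patients with diabetes.

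**All the HbA1c figures are assumed, and nothing shows that prevalence differs between the districts.** This stands too. The working shows sensitivity, not an error known to have occurred.

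**Conclusion.** The point holds as a minor one. As written, the comparison of mean HbA1c mixes patients with and without diabetes, is unadjusted, and sets one district against another. Under the stated assumptions, a 10-point gap in diabetes prevalence shifts it by 0.19 points, with about a 24% chance of a false P<0.05 (22% to 31% over average shares of 70% to 30%). On change from baseline the corresponding figures are about 0.03 points and 6%. The whole-group effect is the effect in diabetes multiplied by the diabetic share, which is a change of question and not a bias. The loss of power from pooling is material on mean values (38% against 62% at a 50% share) and negligible on change (72% against 74%).

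These figures rest on assumed HbA1c means, SDs, effect, diabetic share and prevalence gap, and on an equal split of patients between arms. One secondary outcome is affected; the eGFR analysis is not.

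**What to change.** In the Statistical analysis section, replace the unadjusted t-test on mean HbA1c with a between-group comparison adjusted for month-0 HbA1c. State that the main HbA1c result is the comparison among patients with diabetes at baseline, which ties the planned diabetes subgroup to this outcome. Show HbA1c in the other patients descriptively.

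This takes a sentence or two and no new data: Table 4 already schedules HbA1c at month 0, and diabetes status is established at entry. The price is a smaller n, about 55, 92 or 129 per arm at shares of 30%, 50% or 70% (184 × share). A district difference in prevalence would then no longer move the main HbA1c result. Other differences between the districts still could, because with one district per arm no analysis of HbA1c can separate treatment from district.

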### Sample size

In a previous observational study, the rate of eGFR decline among diabetic patients with overt nephropathy was 4.2 ± 3.8 ml/min/1.73 m^2^ BSA per year [11]. We hypothesized that if the rate of eGFR decline of intervention group is less than control group at least 1 ml/min/1.73 m^2^ per year, the primary outcome of the study will be interpreted as significant. To acheive 80 percent or higher power to detect the difference between the two treatments, it was estimated that 228 stage 3–4 CKD patients were needed to be enrolled to each group [12]. Taking into account that 15% of patients might be loss to follow-up because of non–end point death or other reasons, approximately 250 patients for each group were required.

According to the inclusion and exclusion criteria, recruitment had done in January to June 2011. About 25% of candidates were eligible and asked to participate in the study. The main reason for non-participation was inability of the patient and caregiver to attend the anticipated visits. In July 2011, 433 patients had been enrolled . Enrolled subjects of each group will be further subdivided into 12 patient subgroups with respect to the vicinity of their subdistrict. Each subgroup will consist of 25–30 CKD patients.

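### With one district per arm, continuous outcomes go to unadjusted t-tests and the eGFR slope model is described without covariates, although slope predictors are already collected

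*Protocol article*

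**What the plan says.** Statistical analysis gives one sentence to each method. For the primary outcome: "The comparison of the rate of eGFR decline will be analyzed using linear mixed models", with generalized estimating equations added in brackets. An independent t-test is to "compare mean values and mean differences between intervention and control groups". Categorical variables go to Chi-square or Fisher's exact tests, and clinical endpoints to Cox regression. No baseline covariate is named for any of these. Under Outcomes, age, sex and diabetes appear only as subgroup factors.

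Study design and Interventions fix one district per arm, with patients assigned by where they live. The comparability statement under Interventions concerns hospital facilities. Table 1 gives population, occupation and staffing for each district but no clinical description of the patients. The Limitation section does not mention baseline imbalance.

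**The concern.** Patient numbers do not create balance when only two units are allocated. Eligibility under Enrollment is broad: diabetes or hypertension or both, eGFR 15–59, and protein-creatinine ratio up to 3.5 g/g. Two districts can therefore supply quite different mixes of patients. If the mix differs on something that drives eGFR decline, an analysis that ignores it counts the difference as a treatment effect, or lets it hide one.

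The variables needed to reduce this are already planned: two eGFR values three months apart at screening and diabetes status (Enrollment), protein-creatinine ratio and blood pressure at Visit 1 (Table 4), and age and sex (Outcomes). What is at stake is the credibility of the slope contrast and of every continuous secondary comparison. Covariates chosen only after imbalances have been seen would also be open to challenge.

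**Working it through.** **1. The plan's own figure.** Inputs from Sample size and Statistical analysis: slope SD 3.8 ("the rate of eGFR decline among diabetic patients with overt nephropathy was 4.2 ± 3.8 ml/min/1.73 m^2^ BSA per year"), target difference 1 ("if the rate of eGFR decline of intervention group is less than control group at least 1 ml/min/1.73 m^2^ per year"), "80 percent or higher power to detect the difference between the two treatments", two-sided 5% ("All statistical tests will be two-tailed tests"; "A P-value of less than 0.05 will be considered statistically significant").

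n = 2 × (1.96 + 0.842)² × 3.8² / 1² ≈ 227 per group. The t-test version gives 227.6, so 228. The stated 228 reproduces. The formula treats patients as independent and has no cluster or covariate term.

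**2. Precision implied by that formula.** SE = 3.8 × √(2/228) = 0.356 per year. The smallest significant difference is 1.96 × 0.356 = 0.70 per year.

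**3. Effect of a case-mix gap.** Bias = (difference in share between districts) × (difference in slope between patient types). The documents give neither factor, so both are assumptions. The last two columns use SE 0.356.

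| Share gap | Slope gap (per year) | Bias (per year) | Rejection rate with no true effect, bias in favour | Power for a true difference of 1, bias against |
|---|---|---|---|---|
| 10 points | 1 | 0.1 | 5.9% | 72% |
| 20 points | 2 | 0.4 | 20% | 39% |
| 30 points | 3 | 0.9 | 72% | 5.9% |

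Without bias the last two columns would read 5% and 80%. The sign of any imbalance is unknown.

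**4. Precision gain.** 433 patients were enrolled. The split by arm is not given, so assume an even one with 15% loss: 433/2 × 0.85 = 184 per group. Let the covariates explain a fraction R² of slope variance (assumed), so that SD = 3.8 × √(1 − R²). Power = Φ(1/SE − 1.96).

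- R² = 0: SD 3.80, SE 0.396, power 71%
- R² = 0.1: SD 3.61, SE 0.376, power 76%
- R² = 0.2: SD 3.40, SE 0.354, power 81%

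These figures hold only for independent patients and an even split.

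**5. What adjustment cannot reach.** Take an assumed between-district intraclass correlation with 228 patients per district. The design effect is 1 + 227 × ICC, and the true error of a nominal 5% test is 2 × [1 − Φ(1.96/√design effect)].

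- ICC 0.001: design effect 1.23, error 7.7%
- ICC 0.01: design effect 3.27, error 28%
- ICC 0.05: design effect 12.35, error 58%

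Patient covariates lower this only as far as measured patient mix accounts for the correlation. The rest cannot be separated from treatment.

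**The case against.** The strongest objection is that a covariate list commonly sits in an analysis plan, and this is a condensed article. Mixed, GEE and Cox models all accept covariates, and the text does not say they will be fitted without any. That stands: a reader might infer that the primary analysis is declared unadjusted, and the document does not support this. It does not cover the t-tests, which cannot carry covariates and are a stated choice. Nor does it remove the reason to fix the slope model in advance in a design with one district per arm.

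A slope model with group and time terms also already separates the starting level of eGFR from its rate of decline. That is correct, so a covariate main effect alone would not adjust the slope; the covariate-by-time term is what does so.

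A reader might further infer that recruitment selected patients differently in the two districts, because "The main reason for non-participation was inability of the patient and caregiver to attend the anticipated visits". That sentence gives no breakdown by district, and both arms share the same three-monthly hospital schedule, so differential selection is not shown.

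Finally, ANCOVA is not plainly better than a change score here. With groups that may not be equivalent and a baseline measured with error, it can add bias (Lord's paradox). That also stands, and is why both results should be shown.

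**Conclusion.** The point holds as a recommendation that should be acted on, and not as a demonstrated error in the primary analysis. What is certain is that no covariate is named for any comparison, the t-tests are unadjusted, two allocated districts give no assurance of patient balance, and useful baseline data are collected.

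The size is illustrative only: 0.4 ml/min/1.73 m² per year in the middle case, 40% of the target difference, and 0.1 to 0.9 across the assumed range, in an unknown direction. The power gain (71% to between 76% and 81%) rests on an assumed R², an even split of the 433 patients and the protocol's individual-level formula. It does not describe the real power of a trial with one district per arm.

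It would be wrong to conclude that adjustment repairs the design. Measured patient mix can be reduced; differences between the districts themselves stay fully confounded with treatment.

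**What to change.** Before the data are analysed:

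- **Primary model.** Specify time, group and group × time, plus a short set of baseline covariates, each with its time interaction: diabetes, log urine protein-creatinine ratio at Visit 1, screening eGFR, age and sex. Using the screening eGFR avoids having the Visit 1 value as both covariate and outcome. Report the unadjusted model as sensitivity.
- **Continuous secondary outcomes.** Replace the t-test of change by a baseline-adjusted analysis and show the change-score result beside it, because the arms may not be equivalent.
- **Cox models.** Limit covariates to what the event count supports. The article gives no expected number of events.
- **Limitation.** State that adjustment addresses measured patient case-mix only and that district and treatment remain inseparable.

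If an analysis plan already fixes the slope and Cox covariates, saying so and aligning the Statistical analysis text is enough for those models. No new data are needed. The cost is wording, some extra analysis work and a rule for a few missing baseline values.

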## Discussion

Currently, Thailand has a population of approximately 66 million, in which 55 percent of the population live in rural areas [17,18]. In these areas, the number of specialized personnel is limited and work burden is overwhelming, good clinical care and equal accessibility to the care may be too difficult to achieve. Utilizing renal physicians, or even internists, to take care of CKD patients in rural area is rather far from reality. To combat these problems, we try to search for an appropriate CKD care model which could provide optimal treatment to the rural population. To the best of our knowledge, this study is the first large-scale, community-based cluster randomized controlled trial to study the effect of employing an integrated CKD care which is comprised of multidisciplinary CKD care program in conjunction with well-trained paramedical personnel on delaying CKD progression.

In addition to conventional CKD treatment, the two key processes will be added into the intervention group. Firstly, the multidisciplinary team of district hospital staffs will provide demonstration about essential knowledge CKD care during each hospital visit. We hypothesized that this interactive activity will provide better understanding of essential medical knowledge and increase awareness of burden of CKD and ESRD. The second process is quarterly home visit by the CCN. We trained the CCN and endorsed them to work as the escorts (as the abbreviation name of the study) to protect CKD patients. The important roles of CCN is monitoring compliance to the treatments and instantly feedback to the patients. These important informations will be used to modify lifestyle of CKD patients and may improve compliance to the treatments.

Interestingly, the integration of both processes will increase frequency personnel to patients contact compensating for physician to patient contact time which may improve compliance of drug usage and dietary control; furthermore, the continuity of monitoring might be a key mechanism for sustainable self-behavioral modification. We expect the results of this study will set forth a new standard of community-based CKD care for Thailand.

